### Study endpoints

The endpoints selected in this trial have been utilized by similar trials [10, 14] and are defined within the time window from the date of randomization to death or 12 months, whichever occurs first. The primary endpoint of the study is the number of SREs per arm, which is defined as pathological fractures, spinal cord compression, or interventions (palliative RT, interventional procedures, or spine surgery) at 12 months. The secondary endpoints are as follows:Surrogates of health care cost, including the number and the duration of hospitalizations for SREsPain, as assessed using Brief Pain Inventory (BPI) short-form questionnaireHealth-related quality of life, as assessed using the Functional Assessment of Cancer Therapy-General (FACT-G) and the 5-level EuroQoL-5D (EQ-5D-5L)Median pain-free survival (PFS), defined as the time from study entry to the start of opioids or death. This definition has been utilized on basis of Rosen et al. [10]Median overall survival (OS), defined as the time from study entry to death or censoring due to follow-up

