### Study interventions

All participants in the current study receive systemic therapy as per the standard of care, while arm 2 also receives RT. The specifics of RT, target volume, and organ-at-risk delineation and plan evaluation is performed according to institutional standards. For this protocol, total dose and dose fractionation may be delivered at the discretion of the treating radiation oncologist. All techniques, including conventional, 3D conformal RT (3D-CRT), intensity-modulated RT (IMRT), or SRS techniques may be used, with or without image guidance, as deemed appropriate.

Participants undergo RT to each lesion using one of the dose and fractionation regimens presented in Table 1. A variety of dose fractionation schedules including conventional palliative doses as well as SRS schedules are allowed per protocol. After using appropriate immobilization, a simulation is captured for all participants followed by conduct of a CT or MR imaging in the treatment position. The radiation oncologist determines the utilization, if any, of oral or intravenous contrast.

**Table 1 Tab1:** Dose and fractionation of radiotherapy in the PROMISSED trial

Total dose	Fractions	Dose per fraction	Verification
2000 cGy	5	400 cGy	MV or KV or MR
3000 cGy	10	300 cGy	MV or KV or MR
3000 cGy	5	600 cGy	KV and CBCT or MR
2400 cGy	3	800 cGy	KV and CBCT or MR
2700 cGy	3	900 cGy	KV and CBCT or MR
2400 cGy	2	1200 cGy	KV and CBCT or MR

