Supportive strategies for optimal medical care, including medications for acute RT reactions, are given during the trial at the discretion of the treating physician(s) in bounds of the protocol. These supportive therapies are formally documented as concomitant drugs. Any systemic therapies, such as hormone therapy, chemotherapy, immunotherapy, or targeted therapies, may be given based on the treating physician’s discretion. Pain management in order to help the participant come in position for the RT, but not for long-term control, is allowed to reduce voluntary movement. Opioid pain medications may be used, or their use increased, for positioning study participants for RT as required; however, the participants need to return to the baseline level of pain management after completion of RT. Drugs such as alprazolam are permitted if absolutely required to alleviate the participants’ anxiety or for treatment immobilization purposes. Per-protocol treatment is stopped when there is a systemic or local disease progression leading to enrollment in hospice. If any participants lack the ability or resources to get follow-up CT/MR scans or clinical evaluation, this information is recorded.

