### Schedule of assessments

The full schedule of assessments is described in Table 2. All included participants have objective confirmation of metastatic disease through either standard of care biopsy of a metastatic lesion or a radiology review documenting metastatic disease. Within 8 weeks (56 days) of trial entry, all participants will have had a (1) FDG-PET/CT scan or CT of the chest, abdomen, and pelvis; (2) MRI of the spine with and without contrast; (3) full medical history including comorbidities, current medications, and performance status; and (4) physical exam including vital signs (O_2_ saturation, blood pressure, heart rate, respiratory rate, and temperature), weight, and height. Following randomization, all participants in both study arms are scheduled for follow-up at 1 month (± 2 weeks), 3 months (± 4 weeks), 6 months (± 8 weeks), 12 months (± 12 weeks), and 24 months (± 16 weeks) and receive the following assessments: clinical evaluation, assessment of performance status, imaging studies, evaluation of AE (CTCAE v5.0) for individuals in arm 2, BPI Short Form, and EQ-5D (Table 3).

**Table 2 Tab2:** Schedule of assessments in the PROMISSED trial

Assessments*	Pre-enrollment	Baseline	Treatment	1-month F/U^1^	3-month F/U^1^	6-month F/U^1^	12-month F/U^1^	24-month F/U^1^
Informed consent	X							
Eligibility verification	X							
Physical exam	X^2^				X	X	X	X
Medical history	X^2^							
Performance status		X^3^			X	X	X	X
Skeletal related events (SREs)^4^								
Lesion identification worksheet^5^		X						
Numeric pain rating scale (NPRS)	X^6^		X^8^	X^9^	X	X	X	X
Neurological exam	X^6^				X	X	X	X
Imaging of the spine (MRI preferred, acceptable alternates include CT scan or bone scan)	X^7^				X	X	X	X
Documentation of patient’s pain medication^10^	X^6^							
BPI (QL)^11^		X			X	X	X	X
FACT-G (FA)^12^		X			X	X	X	X
EQ-5D (HP)^13^		X			X	X	X	X
Adverse event (AE) evaluation			X	X	X	X	X	X

*All the assessments will come from randomization. Therefore, both arms (arms 1 and 2) have the same timelines

^1^From randomization (times will be the same for intervention and without intervention) treatment. The window for the follow-up visits will be (1) 1 month ± 2 weeks; (2) 3 months ± 1 month; (3) 6 months ± 2 months; (4) 12 months ± 3 months; (5) 24 months ± 4 months

^2^Within 4 weeks before registration. Registration is considered when the eligibility is signed by the investigator

^3^Performance status can be collected before consent

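### Pain-free survival counts temporary opioids permitted for RT positioning as failures, mainly in arm 2, and the 12-month endpoint window conflicts with the definition of overall survival

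*Protocol article*

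**What the plan says.** **Pain-free survival.** Study endpoints lists median pain-free survival, "defined as the time from study entry to the start of opioids or death". Nothing is said about the indication or duration of the opioid. Planned statistical analysis compares it between arms with a log-rank test.

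**Permitted opioids.** Study interventions states: "Opioid pain medications may be used, or their use increased, for positioning study participants for RT as required". The same paragraph says that this is not for long-term pain control and that "the participants need to return to the baseline level of pain management after completion of RT".

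**Who receives RT.** "All participants in the current study receive systemic therapy as per the standard of care, while arm 2 also receives RT". In arm 1, palliative RT can occur, but only as later treatment, where it is itself a component of the SRE endpoint.

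**Time window.** Study endpoints opens by saying that the trial's endpoints "are defined within the time window from the date of randomization to death or 12 months, whichever occurs first". The same section then gives median overall survival, "defined as the time from study entry to death or censoring due to follow-up", with no 12-month limit. Schedule of assessments has visits up to 24 months.

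**The concern.** Two rules in the same article collide. Study interventions treats a positioning opioid as procedural and temporary, with a return to the earlier level of pain management. Study endpoints counts the same drug as the end of pain-free survival. Eligible spine metastases do not require opioids at entry, so for many participants a positioning opioid would be the first opioid started. Because protocol RT exists only in arm 2, these events fall early and mostly on one side. The definition creates the imbalance after assignment, so randomisation cannot remove it. The result is a bias against RT on a named secondary endpoint.

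The window raises a smaller issue. On the introductory sentence, deaths and opioid starts in the second year do not count. On the definition of overall survival and the visit schedule, they do. The article supports both readings, and the choice decides whether a median is likely to be observed. The time origin also differs (randomization for the window, study entry for the two survival endpoints), which is minor because Table 2 runs all assessments from randomization.

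**Working it through.** **1. The plan's own figure.** The article gives no design figure for pain-free or overall survival. Its only sample size is for SREs: 60% versus 30%, one-sided 0.05, power above 80%. With pooled proportion 0.45:

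n per arm = [1.645·√(2·0.45·0.55) + 0.842·√(0.6·0.4 + 0.3·0.7)]² / 0.30² = (1.157 + 0.565)² / 0.09 ≈ 32.9, so 33 per arm and 66 in total.

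66/0.9 = 73.3, so 74, or 37 per arm. The figure reproduces and does not depend on this point.

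**2. Effect on the arm 2 median.** Let a fraction f of arm 2 start a positioning opioid in the first month, and let true times be exponential with rate λ. After that month arm 2 pain-free survival is (1 − f)·exp(−λt), so the median is ln[2(1 − f)]/λ. Assume a control median of 6 months and a hazard ratio of 0.5, so λ = ln 2/12 = 0.0578 per month:

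- f = 0: 12.0 months
- f = 5%: ln(1.9)/0.0578 = 11.1 months
- f = 10%: ln(1.8)/0.0578 = 10.2 months
- f = 20%: ln(1.6)/0.0578 = 8.1 months

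**3. Effect on the log-rank test.** Simulated trials used 37 per arm, exponential times, two-sided 0.05, and positioning opioids placed within the first month. Every rate here is an assumption, because the article gives none. Scenario A has a control median of 6 months and 24 months of follow-up.

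| Share of arm 2 with a positioning opioid | Power for RT, true hazard ratio 0.5 | Significant against RT, no true effect |
|---|---|---|
| 0% | about 77% | 2–3% |
| 2% | 75% | 3% |
| 5% | 66% | 4% |
| 10% | 57% | 7% |
| 20% | 31% | 13% |

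A repeat with 6,000 trials per cell agreed to within about 2 percentage points (15% in the last cell).

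Scenario B has a control median of 9 months, a cut-off at 12 months and a true hazard ratio of 0.6. At 0%, 5%, 10% and 20% use, power is 34%, 24%, 14% and 4%. With no true effect, significant results against RT occur in 2.5%, 4.5%, 8% and 19% of trials. Excluding positioning opioids returns both scenarios to the 0% row.

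**4. Overall survival within 12 months.** A median exists by 12 months only if 12-month survival S is 50% or lower. The article gives follow-up, not survival: 60–80% followed for at least a year (Power calculation), or nearly 60% (Planned statistical analysis). Taking those shares as survival is an assumption. The exponential median is 12·ln 2/(−ln S), and the last column is a binomial tail for at least 19 deaths among 37.

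| S at 12 months | Median (months) | Chance that at least half of an arm of 37 dies by 12 months |
|---|---|---|
| 0.80 | 37.3 | <0.1% |
| 0.70 | 23.3 | 0.5% |
| 0.60 | 16.3 | 11% |
| 0.50 | 12.0 | 50% |
| 0.40 | 9.1 | 89% |

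**The case against.** **The definition follows a prior trial and is objective.** The article says that its definition of pain-free survival comes from an earlier randomised trial in bone metastases. Any opioid start is easy to ascertain. Deciding that an opioid was solely for positioning is a judgement made in an open-label trial, almost always in arm 2, and could tilt the result towards RT. This stands as a cost of the remedy. It does not defend the current rule, whose bias in the other direction is built in.

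**It could be left to the analysis plan.** Event-coding detail often is. Here, however, the article fixes a rule and permits something that the rule misclassifies, so the conflict is on the page.

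**The size may be small.** Participants are asymptomatic or minimally symptomatic, so use may be rare. At 2% the loss is slight. A reader might take the fall to 31% as the expected effect, but it belongs to one assumed rate at the top of the range shown.

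**Stronger readings that the article does not support.** A reader might infer that every participant enters free of opioids. Inclusion criteria says only that the spinal metastases do not require them, and the allowance for increased use suggests that some participants may already take one. A reader might infer that arm 1 cannot have such an event, but palliative RT is possible there. A reader might also infer that median overall survival cannot be reached and that second-year deaths are discarded. The specific definition of overall survival is open-ended, and the 12-month window is repeated only for SREs. If about 60% really are alive and under observation at 12 months, the curve stays near or above 60%. That is an approximate planning figure for follow-up, not a survival estimate by arm. A log-rank test censored at 12 months would also remain valid without a median.

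**Conclusion.** The point on pain-free survival holds. As written, a permitted and temporary procedural opioid is an endpoint event, it falls early and mainly in arm 2, and it biases the log-rank comparison against RT. The direction follows from the text. The size does not, because it depends on an unstated rate of use: slight at 2%, material from about 5–10%, and severe at 20%, under exponential times and the assumed medians and hazard ratios.

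The point on the window holds as an inconsistency to be resolved. The supportable statement is that a median overall survival may well not be reached within 12 months. Both matters concern secondary endpoints and should be corrected; the primary endpoint and the sample of 74 are unaffected.

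**What to change.** Reconcile Study endpoints with Study interventions in the endpoint definition alone, leaving permitted medication as it is:

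- State that an opioid documented at prescription as given for RT positioning, and stopped with a return to baseline pain management after RT, is not a pain-free-survival event in either arm.
- State how the start of opioids applies to a participant already taking one at entry.
- Report the any-opioid definition as a sensitivity analysis, because attribution of the reason is unblinded.
- Apply the 12-month window only to SREs and SRE hospitalisations.
- Analyse pain-free and overall survival from randomisation through all available follow-up.

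The cost is a few sentences and one added data item, the reason for starting an opioid. Pain medications are already collected (Table 2, note 10) and supportive drugs are already documented. The rule should be fixed before outcome data are examined, so that no event is reclassified with knowledge of the results.

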### Rationale for study instruments and endpoints

This trial is investigating the impact of early, upfront RT on the number of SREs occurring in participants with high-risk spine metastases. The clinical rationale for using SREs as the primary endpoint has been addressed previously and is further expanded here. It has been demonstrated that once a patient’s spinal metastases become severely symptomatic, it is significantly more difficult to return the patient to a low pain burden with treatment compared to when the lesions were less symptomatic [7]. Additionally, in a recent multicenter study that aimed to describe differences in health resource utilization of SREs across Europe and the USA, nearly 25% of reported SREs were found to warrant inpatient hospitalization with a mean length of stay of 18 days [12]. In this work, over 95% of SREs led to procedural management, of which bone RT was the most frequent. Similarly, another investigation demonstrated that nearly a quarter of all SREs warranted an inpatient admission with a mean length of stay of 19.5 days [13]. Furthermore, it has also been demonstrated that efforts to prevent SREs from occurring considerably lead to cost-reduction related to managing SREs, given the substantial economic cost of interventions warranted [11]. Finally, these events also lead to significant utilization of health resources and a major socioeconomic burden [12, 13]. Therefore, on basis of their clinical, economic, and patient-centric utility, SREs have been chosen as the primary endpoint.

Regarding secondary endpoints, the use of median OS as an outcome measure is widely considered standard in oncology. The rationale for other endpoints follows. The use of median PFS has been based as per the key RCT in bony metastases by Rosen et al. [10]. The assessment of pain, and its impact on the participant, is planned for capture through the BPI, a validated self-reported outcome measure [18]. Spinal origin pain has been shown to affect all domains of the individual’s quality of life. BPI short-form, a 17-item scale, captures information regarding pain severity, pain location, chronicity, degree of relief secondary to therapy, use of pain medications, depression, suffering, and perceived availability of relief, among other aspects. BPI’s validity and reliability has been previously demonstrated, and it has been used in several prior RT trials, including the Radiation Therapy Oncology Group (RTOG) 97-14 [18–20]. BPI asks individuals to score their pain for the last week at its “worst,” “least,” “average,” and “now.” The scale is from 0 to 10, with the typical standard deviation for the item “worst pain” being 2.4 in populations with cancer [18]. Thus, a one-point difference in “worst pain” may be considered a minimum clinically important difference (MCID). Mild pain corresponds to a BPI score of 1–4, moderate pain corresponds to a score of 5–6, and severe pain corresponds to a score of 7–10. BPI also asks individuals to estimate other sensory and reactive components on a similar scale of 0–10.

The study also plans to use FACT-G version 4.0 as an instrument to capture the health-related quality of life, given that pain assessment is closely impacted by and impacts the former. This outcome measure has been utilized previously in radiotherapy trials as well, including the RTOG 97-14 [20]. FACT-G was developed and reported by Cella and colleagues in 1993 [21]. It is a 27-item questionnaire, with each item scored on a 5-point Likert scale (from “not at all” to “very much”). The questionnaire captures information across four domains: physical well-being (7 items), social/family well-being (7 items), emotional well-being (6 items), and functional well-being (7 items). The questionnaire has been reported to have high test-retest reliability and validity, and normative data regarding the same are available both from the general US population and in the US cancer population [22]. FACT-G has also been mapped to EQ-5D [23].

EuroQoL 5-Dimensions (EQ-5D) is a widely utilized family of patient-reported instruments designed to capture and value health. These five dimensions are mobility, self-care, usual activities, pain/discomfort, and anxiety/depression. EQ-5D’s use as an outcome measure is recommended by several health technology assessment authorities [24, 25]. The 3-level EQ-5D (EQ-5D-3L) asks individuals to rate each of the five dimensions across three levels, while the EQ-5D-5L, introduced in 2009, does this for five levels [24, 26]. Whereas the FACT-G is a cancer-specific instrument, the EQ-5D is a two-part, generic preference-based outcome measure.

### Assessment of safety

With regard to the assessment of the safety of the intervention, adverse events (AE) will be defined as any untoward medical occurrence associated with the use of an intervention in humans, whether or not considered intervention-related (21 CFR 312.32 (a)). All AEs will have their relationship to study intervention assessed by a clinician, who will examine and evaluate the participant based on temporal relationship and their clinical judgment. Only AEs that are definitely, probably, or potentially related to the protocol treatment will be reported. AEs will be classified according to the NIH Common Terminology Criteria for Adverse Events (CTCAE) version 5.0.

### Power calculation

Power calculation has been performed by a formally trained institutional biostatistician, based on the primary endpoint of the rate of SREs from the date of participant randomization to their death or 12 months follow-up, whichever occurs first, in the two trial arms. SRE, a composite outcome measure, has been defined as a pathological spine fracture, spinal cord compression, or warranting of a procedure (palliative RT, interventional procedures, or spine surgery). SRE is a binary variable, where the event rate may be defined as the number of spine lesions with SRE occurrence divided by the total number of target spine lesions identified. Given the lesion-based analysis in the current trial, occurrence or non-occurrence of an SRE at one vertebra does not impact the status of other spine lesions within the same individual.

Based on institutional records and previous trials, it is estimated that nearly 60–80% of patients may be successfully followed up for at least 1 year. For the standard of care trial arm, where only routine medical management is done, the rate of SRE is known to be nearly 60% within 1 year. Meanwhile, it is known that approximately three fourths of inpatient radiation consultations for painful bone metastases have been reported to lead to palliative RT. Furthermore, prior studies indicate that nearly 60% of RT-targeted spine lesions had been diagnosed ≥ 4 months prior to RT [7]. Therefore, we believe a 60% estimated event rate (as defined above) at 1 year is a conservative estimate. For the investigational trial arm, where early prophylactic RT is being provided to high-risk spine metastases, an SRE rate of 30% is estimated. The efficacy of RT in controlling pain from spine metastases is well-known. Since RT targets and mitigates, to a certain extent, the pathologic effect of a spinal metastases, this leads to reduced development of major bony pain, which is often a causative factor for SREs. For these SRE rates, inclusion of at least 66 individuals with evaluable SRE endpoints in a 1:1 randomization will allow the trial to achieve > 80% power based on a one-sided, two-sample proportion test with significance level of 0.05. Given that the individuals who withdraw prior to the SRE endpoint occurring may not evaluated as per the trial plan; therefore, a per-protocol analysis will be carried out. The limitations of the per-protocol analysis are mitigated by the use of hard endpoints in the current study along with the high morbidity and dismal prognosis of the participants. In order to ensure a minimum of 33 participants are enrolled per trial arm, we plan to over-accrue by 10%, so that the trial is sufficiently powered for the primary endpoint, resulting in a planned sample size of *N* = 74 participants. Additionally, we note that the unit of analysis is the spine lesion, and a small subset of patients may have multiple evaluable lesions (SREs). Since each lesion will be included separately in the analysis, therefore, the final sample size for the primary endpoint may be higher than estimated. We expect to enroll all 74 participants within 2 years.

Furthermore, the investigational arm is unlikely to result in significantly more deaths, since palliation of symptomatic spine metastases is typically performed as part of routine care using RT. This treatment modality is widely utilized and well-established in this patient population and is highly unlikely to have more toxicity.

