**Methods:**

This is a single-center, parallel-arm, in-progress RCT in adults (≥ 18 years) with ECOG performance status 0–2 and asymptomatic or minimally symptomatic (not requiring opioids) high-risk spine metastases from histologically confirmed solid tumor malignancies with > 5 sites of metastatic disease on cross-sectional imaging. High-risk spine metastases are defined by the following: (a) bulkiest disease sites ≥ 2 cm; (b) junctional disease (occiput to C2, C7-T1, T12-L2, L5-S1); (c) posterior element involvement; or (d) vertebral body compression deformity > 50%. Patients are randomized 1:1 to receive either standard-of-care systemic therapy (arm 1) or upfront, early radiotherapy to ≤ 5 high-risk spine lesions plus standard-of-care systemic therapy (arm 2), in the form of 20–30 Gy of radiation in 2–10 fractions. The primary endpoint is SRE, a composite outcome including spinal fracture, spinal cord compression, need for palliative radiotherapy, interventional procedures, or spinal surgery. Secondary endpoints include (1) surrogates of health care cost, including the number and duration of SRE-related hospitalizations; (2) overall survival; (3) pain-free survival; and (4) quality of life. Study instruments will be captured pre-treatment, at baseline, during treatment, and at 1, 3, 6, 12, and 24 months post-treatment. The trial aims to accrue 74 patients over 2 years to achieve > 80% power in detecting difference using two-sample proportion test with alpha < 0.05.

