Early palliative treatment has been demonstrated to improve the quality of life and even survival for patients with metastatic cancer [6]. Many specialized centers now advocate for earlier integration of RT in a patient’s treatment course, especially with patients living longer with their systemic disease. While several RCTs have evaluated the efficacy and safety of varying RT regimens for managing symptomatic bone lesions, few studies so far have examined the utility of early, upfront RT for the treatment of asymptomatic or minimally symptomatic spine metastases. It is however known that RT can significantly reduce the risk of SREs in patients with solid tumors metastasizing to the bone [14]. A phase 2, multicenter randomized controlled trial recently evaluated the role of early prophylactic RT in patients with high-risk bone metastases, including spine metastases, in patients with polymetastatic disease [14]. In this study, 78 patients with 122 high-risk bone metastases were enrolled and randomized to systemic therapy or observation, in addition to early prophylactic RT. At 1 year, SREs occurred in 1 of 62 lesions (1.6%) in the RT arm and 14 of 49 lesions (29%) in the standard-of-care systemic therapy arm (*P* < 0.001). Specific high-risk features were associated with a significant difference in the time-to-SRE, with most SREs seen in junctional or bulky (> 2 cm) spine disease (*P* = 0.016). Given this intriguing signal, the primary aim of the current randomized trial is to determine whether upfront, early palliative or pre-emptive RT, compared to standard-of-care systemic therapy in patients with high-risk asymptomatic or minimally symptomatic (non-opioid dependent) spine metastases leads to fewer SREs.

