### Planned statistical analysis

The primary objective of this study is to compare the rate of SREs from the date of randomization to mortality or 1 year, whichever occurs first, between participants receiving standard of care therapies versus participants receiving palliative RT for high-risk spine metastases. It is expected that nearly 60% of the enrolled participants will have at least 1 year of follow-up. The primary endpoint, SRE, has been previously defined as a composite measure including pathological spine fractures, spinal cord compression, or need of spinal interventions (palliative RT, or orthopedic surgery). SRE is a binary variable, with the rate of SRE defined as the number of lesions having SRE divided by the total number of eligible spine lesions. Given that this analysis is lesion-based, not participant-based, therefore, occurrence or non-occurrence at one lesion does not impact the status of other lesions in the same participant. Around 15% of participants may have multiple lesions, for which each lesion gets evaluated as an independent unit of analysis. Meanwhile, unlike the primary objective, the secondary objectives will be evaluated per participant.

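### The stated power above 80% is not supported by the plan's own inputs: it allows for 10% loss but expects only 60–80% one-year follow-up, and its 60% per-lesion control rate is not shown to be cautious

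*Protocol article*

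**What the plan says.** The Power calculation section assumes SRE rates at 1 year of 60% (standard of care) and 30% (early RT). It derives 66 individuals with evaluable endpoints, 33 per arm, for power above 80%, "based on a one-sided, two-sample proportion test with significance level of 0.05". To protect that number, "we plan to over-accrue by 10%, so that the trial is sufficiently powered for the primary endpoint", which gives N = 74.

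On follow-up, the same paragraph estimates that "nearly 60–80% of patients may be successfully followed up for at least 1 year". The Planned statistical analysis section gives only the lower end: "It is expected that nearly 60% of the enrolled participants will have at least 1 year of follow-up". The power section adds that individuals who withdraw before an SRE may not be evaluated and that the analysis will be per-protocol. Under Study endpoints, the window runs from randomization to death or 12 months, whichever is first.

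On the control rate: "Therefore, we believe a 60% estimated event rate (as defined above) at 1 year is a conservative estimate". The definition referred to is lesions with an SRE divided by target lesions. The Background reports, from the earlier trial of prophylactic RT, SREs in 1 of 62 lesions (1.6%) with RT and in "14 of 49 lesions (29%) in the standard-of-care systemic therapy arm". The roughly 65% one-year rate, also in the Background, is given for patients.

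The Abstract states power above 80% "using two-sample proportion test with alpha < 0.05", without saying one-sided.

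**The concern.** A 10% allowance covers the loss of about one patient in ten, while the plan expects two to four in ten not to reach one year. If those patients drop out of the primary analysis, the trial falls below the number on which its power rests. The control rate matters for the same reason. It is expressed per lesion, yet the one per-lesion control figure in the document is about half of it, and the RT-arm rate assumed here (30%) is roughly that trial's control-arm rate.

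At stake is how a null result is read. With a stated power above 80% it would pass as evidence against a 30-point reduction, when the real chance of detecting that reduction may have been nearer two in three.

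**Working it through.** **Inputs from the document.** Control 60%, RT 30%; one-sided 0.05; 66 evaluable; 10% over-accrual, N = 74; one-year follow-up 60–80%; about 15% of participants with multiple lesions; earlier trial 14/49 and 1/62 per lesion.

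**Formula.** Two-proportion test with pooled variance under the null, n per arm:

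power = Φ{ [ |p1 − p2|·√n − 1.645·√(2·p̄(1−p̄)) ] / √(p1(1−p1) + p2(1−p2)) }, with p̄ = (p1 + p2)/2.

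For 60% versus 30%: p̄ = 0.45, √(2 × 0.45 × 0.55) = 0.7036, √(0.24 + 0.21) = 0.6708.

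**1. The plan's own figure reproduces.** n = 33: (0.3·√33 − 1.645 × 0.7036)/0.6708 = 0.844, so power is 80.06%. At 32 per arm it is 78.9%. Over-accrual: 66/0.9 = 73.3, rounded to 74 (37 per arm). Since 66/74 = 89.2%, the plan tolerates 10.8% unevaluable.

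**2. Only patients with one-year follow-up are evaluable.** 74 × 0.60 = 44.4 and 74 × 0.80 = 59.2.
- 22 per arm: 64.5%
- 29.6 per arm: 76.1%

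Enrolment that would yield 66 such patients: 66/0.80 = 82.5 (83) to 66/0.60 = 110.

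**3. All attrition is death, kept as a non-event.** Assumptions: constant hazards, and 60/30 are the rates that would be seen without deaths. With h = −ln(1 − p) and d = −ln(1 − mortality), the observed rate is h/(h + d) × (1 − e^−(h+d)).
- 20% mortality: 54.7% versus 27.1%; power at 37 per arm 78.9%
- 40% mortality: 48.8% versus 23.8%; power at 37 per arm 72.8%

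**4. All attrition is withdrawal, but SREs before loss are counted.** Same hazards.
- 20% loss: about 63 evaluable, power 79.2%
- 40% loss: about 51 evaluable, power 72.2%

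**5. All 74 evaluable, and 60/30 already net of death.** n = 37: (0.3·√37 − 1.645 × 0.7036)/0.6708 = 0.995, power 84.0%.

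**6. Extra lesions.** Steps 1–5 use one lesion per patient, as the plan's calculation does. Suppose 15% of patients have two lesions each (assumed; the number is not given). At 44–59 patients, power is then 70–81% if lesions within a patient are independent and 66–77% at an intra-patient correlation of 0.5. With five lesions each, the protocol maximum, it is 83–91% if independent but 66–77% at a correlation of 0.3.

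**7. Control rate.** 14/49 = 28.6%, and 60/28.6 = 2.1. Power at a control rate of 28.6%:

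| RT rate | 22 per arm | 33 per arm |
|---|---|---|
| 1.6% (earlier trial) | 82% | 94% |
| 5% (assumed) | 68% | 83% |
| 10% (assumed) | 47% | 61% |
| 14.3% (halved, the plan's own ratio) | 31% | 41% |

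At 33 per arm, power stays at 80% or more only if the RT rate is about 5.8% or lower.

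**The case against.** **A reader might infer that the trial will have only 44–59 evaluable patients, so that its power is shown to fall short.** The document does not support that. One-year follow-up is not the same as evaluability: a death closes the endpoint window, and a patient with an SRE who is later lost still counts. So 44–59 is a floor, and the 20–40% is not split into deaths and losses. On one reading, the 60% is defined up to death or 12 months and so already allows for deaths. Deflating it again, as in step 3, would then count mortality twice. This objection stands and is why the upper end of the range is 84%. It does not rescue the stated figure, because the plan never says that nearly all attrition is death or that its rates are net of death. Steps 3 and 4 fall below 80% at both ends of the plan's own follow-up range.

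**The plan says multiple lesions may raise the sample size.** True, but the gain shrinks with correlation within patients (step 6).

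**A reader might infer that a 29% control rate means low power.** It does not: with both rates of the earlier trial, power is 94% at 33 per arm and still 82% at 22. The 41% combines that trial's control rate with the present plan's ratio. That trial also covered all high-risk bone sites, with most SREs in junctional or bulky spine disease, so a spine-only rate could differ from 29%. What stands is narrower: nothing shown supports calling 60% per lesion conservative. The share of consultations leading to RT, and the time since diagnosis among irradiated lesions, are not SRE rates in untreated lesions.

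**A reader might infer that the Abstract contradicts the power section on sidedness.** It does not. It condenses, and the power section is explicit. The two-sided power of 69.6% at 33 per arm describes a test that the plan does not propose. The omission is worth correcting only because a reader of the Abstract alone could take the test as two-sided.

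**Conclusion.** The concern holds in this form: power above 80% is not supported by the plan's own inputs. The sample size reproduces exactly but has no reserve, and the 10% allowance does not fit 60–80% follow-up when withdrawals before an SRE may be left out. For 60% versus 30%, one-sided 0.05 and one lesion per patient, power runs from about 65% (completers only, 60% follow-up) to 84% (all 74 evaluable, rates net of death). The intermediate 73–79% for deaths kept as non-events rests on constant hazards and on 60/30 being rates absent death. Separately, the 60% control rate is 2.1 times the only per-lesion control rate cited. This leaves the word conservative without support but does not by itself show a loss of power.

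**What to change.** Keep N = 74 and make these changes in the Power calculation section, the Planned statistical analysis section and the Abstract:

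1. State how deaths before an SRE and losses before an SRE count in the primary endpoint, and whether 60% and 30% already allow for death. Reconcile the 10% allowance with the 60–80% follow-up on that basis.
2. Replace the single claim of more than 80% with the resulting range by scenario, about 65% to 84%.
3. Remove the description of 60% as conservative. Give a short power table over per-lesion control and RT rates spanning 29%/1.6% to 60%/30%.
4. Write one-sided 0.05 in the Abstract.

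The cost is wording and a small table, and the stated power becomes less favourable. No extra patients and no change of primary analysis are required.
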